**Investigators: [name], [name], [name]**

**Washington University in St Louis**

**Background:**

Hypoxic-Ischemic injury in the newborn occurs at a rate of 1-3.5/1000 live births and carries with it a significant morbidity and mortality [1]. As many as 20% die in the neonatal period and 35% of survivors experience significant long term neurodevelopmental disability [2]. While advances in management have resulted in improved survival, morbidity has not significantly changed in the last several decades. One mechanism of neuronal injury in hypoxic ischemia is oxidative stress from inflammation and free radical production [3]. These oxygen free radicals overwhelm antioxidant defenses and results in widespread injury through lipid peroxidation. The brain, both in the adult and the neonate has been a focus of much interest given it inherent vulnerability to oxidative stress, limited antioxidant defenses, and high level of aerobic metabolism [4]. Often by the time an infant with hypoxic ischemic brain injury presents these inflammatory processes are underway making intervention difficult. Even mild hypothermia, the latest treatment modality, only affects the secondary phase of neuronal death when inflammatory processes are already underway. Therefore, the impact of any neuroprotective strategy that is started ex-utero is limited in its potential benefit. To curtail the inflammatory process and thus improve outcome from hypoxic ischemic injury an intervention would need to be initiated prior to the insult. This requires a shift in treatment strategy that focuses on the fetus rather than the ex-utero newborn.

***Criteria for neuroprotectant***

Predicting which fetuses carry the most significant risk of developing hypoxic ischemic injury is difficult and not possible prenatally. To intervene prior to injury a large number of pregnant women would have to be treated in order to incur benefit to only a handful of newborns. Therefore, the ideal neuroprotective candidate is one that can not only head off the mechanism of injury, but also meets criteria for widespread implementation. These criteria include safety to the women and their fetus, easily tolerability to ensure compliance, and economic feasibility.

***Polyphenols***

One potential neuroprotective candidate is the class of chemicals known as polyphenols. These natural antioxidants are found in a whole host of foods such as berries, nuts, grapes, chocolates, and teas. Defined as having at least one phenolic group per molecule, these diverse group of non-traditional nutrients have been studied and found protective in a whole host of human diseases ranging from cardiovascular disease and erectile dysfunction to neurodegenerative diseases such as Parkinson’s and Alzheimer’s [4-9]. Studies have shown that these polyphenols can cross the blood brain barrier and exert their effects directly on the brain [10, 11].

One of the highest polyphenol containing dietary supplements commercially available is pomegranate juice (PJ) which has been studied both in vitro and in vivo as a potential antioxidant without any proven side effects [6, 12, 13]. Studies in animal models of hypoxic ischemic injury have shown that maternal supplementation with polyphenols through pomegranate juice greatly improves neurologic injury [14, 15]. Loren et al. in 2005 showed that maternal intake of PJ during the last third of pregnancy in mice lead to a > 60% reduction in brain tissue loss following hypoxic-ischemic insult. This correlated with a decrease in overall caspase-3 activation (apoptosis) on pathology. Higher levels of ellagic acid, a polyphenic component, were found in the plasma of the intervention group, documenting placental transmission. This same research group in 2007 demonstrated that this neuroprotection is specific to polyphenols and is only present when given prior to the insult. Therefore, infants with hypoxic ischemic injury may indeed benefit from supplementation with systemic antioxidants such as polyphenols, but it would likely have to be administered prenatally before any insult occurred. Because predicting potentially at risk infants is not possible, no study to date has looked at maternal polyphenol administration as a potential neuroprotectant to at risk newborns.

***A potential model***

To properly test if in utero polyphenol administration can mediate antioxidant defenses and protect against hypoxic ischemia, one would need a model of brain injury that could be predicted prenatally. Intrauterine growth restriction (IUGR) is defined as fetal growth in utero that fails to meet its potential. The threshold for this inadequate growth varies depending on the source, but generally is defined as weight below the 10th percentile of the general population for the specific gestational age of the fetus.

Fetuses with impaired intrauterine growth often suffer from long term placental insufficiency and subsequent chronic hypoxia not dissimilar from infants suffering from acute perinatal injury with subsequent hypoxic ischemic injury. Many IUGR infants tend to not tolerate labor secondary to their inability to withstand the transient drops in placental blood flow that accompanies normal labor. As a group these infants are twice as likely to have low apgar scores, twenty times more likely to suffer from encephalopathy, five times more likely to suffer perinatal stroke, and ten times more likely to die in the neonatal period [16-18]. Furthermore, these fetuses have a 2 to 3 fold increased risk of delivering prematurely placing them at additional risk of long term morbidity and mortality [19]. MR imaging in premature infants suffering from IUGR show decreased intracranial volume, abnormal diffusion of the posterior limb of the internal capsule, decreased cerebral gray matter, and reduced hippocampal volume that persists through term when compared to gestational aged matched controls [20, 21]. Magnetic resonance spectroscopy in these infants displays elevated lactate and creatine in the white matter, further indicating hypoxemic and nutritional injury. In long term neurodevelopmental follow up patients born with IUGR have an increased risk of developing cerebral palsy and continue to have deficits in learning, cognition, and attention up through adolescence [22-28]. These findings are more pronounced when focusing on the more severe end of the IUGR spectrum, those with evidence of abnormal umbilical flow (absent or reversed end diastolic flow) or birth weight < 3rd percentile [29-31]. This central nervous system injury is likely mulifactorial, with mechanisms such as altered placental flow, repeated hypoxemia, elevated cortisol levels from alterations of the hypothalamic-pituitary-adrenal (HPA) axis regulation, nutritional deprivation, and acidosis after birth all contributing [18, 32]. Given that the majority of infants with IUGR are diagnosed prenatally by standardized ultrasound measurements (usually end of the 2nd trimester) this population represents an ideal model for testing the impact of a prenatal neuroprotectant.

Preliminary studies in our laboratory have been undertaken in two phases of a previously approved protocol (IRB #201111063). The first phase was undertaken with healthy pregnancies in their last three weeks of pregnancy taking 8oz of pomegranate juice to ensure that it crossed the placenta. In this study, we confirmed placental transfer of polyphenols with HPLC detectable maternal and cord blood levels rising after two weeks on pomegranate juice. In addition, placenta from 4 women who received pomegranate juice in their last 2 weeks of pregnancy demonstrated decreased expression of heat shock proteins (HSP) in the pomegranate group as compared to controls. For phase II of this study (IRB #201111063) we randomized 41 mothers who were pregnant with infants with a diagnosis of IUGR by fetal ultrasound to receive 8oz pomegranate juice or 8oz apple juice. We were able to undertake MRI scans in 30 infants due to problems with preterm birth or movement on the MRI. On this analysis, the infants born to pregnant mothers who drink 8 oz of pomegranate juice daily in the last trimester of pregnancy demonstrated improved diffusion measures in the brain of their newborn infant representing more mature white matter microstructure and improved brain growth (see figures 1-6 below). Of importance, none of the mothers in the IUGR study had placental examination to determine the possible mechanism of benefit of pomegranate juice in pregnancies complicated by IUGR. This current study will fill this important gap in our knowledge.

[figure not shown]
Figure 1: Pilot data in IUGR Trial in 41 mothers randomized to receive pomegranate or apple juice

[figure not shown]

[figure not shown]
Figure 2: Placental pathology with expression for Heat Shock Protein (HSP 90) in women following labor who received 8 oz of promegranate juice compared to control in women without IUGR.

Figure 3: Cord blood levels of polyphenols at the time of birth in women in the randomized trial who received pomegranate juice (pink) or apple juice (yellow). Note the marked elevation in the levels of two polyphenols in the cord blood of infants whose mothers received pomegranate juice.

[figure not shown]

[figure not shown]

[figure not shown]

[figure not shown]
Figure 4: Brain diffusion measures were sampled in the infant brains at term equivalent. demonstrating decreased Anterior Limb of Internal Capsule diffusivity (p<0.05); increased left Frontal Lobe anisotropy (p<0.05) and trend to decreased diffusivity (p=0.07); and decreased left centrum Semiovale diffusivity (p<0.05). These changes are consistent with a more mature white matter in the infants whose mothers received pomegranate juice.

Figure 5: Brain Metrics representing brain growth demonstrated that infants who had pomegranate exposure in their mothers had larger biparietal diameters (3a) and smaller interhemispheric distances (5) and interopercular distances (4a, 4b) representing better brain growth and less extra-axial space than infants whose mothers received apple juice.

[figure not shown]

The present study seeks to investigate the impact of maternal dietary supplementation with pomegranate juice or its extract on the placenta and newborn brain development and function. This study will uniquely undertake concurrent examination of placentas and infant brain outcomes to examine the mechanism of potential benefit in IUGR.

**Hypothesis:** Maternal consumption of pomegranate juice in the last trimester of pregnancy will result in improved newborn brain development and placental function compared to infants with mothers who consume a placebo.

**Specific Aim:** To study the impact maternal polyphenol rich PJ administration has on placental function; brain injury and development (by MRI) at term and neurodevelopmental outcome at 18-24 months in infants with IUGR.

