**Inclusion criteria:**

- Expecting mother with a fetal diagnosis of intrauterine growth restriction (IUGR) defined by estimated birth weight ≤ 10th percentile for gestational age and gender based on the Alexander growth curves.
- ≥ 6 weeks from expected due date.

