**Study plan:**

Dating will be by ultrasound or reliable clinical dating by ACOG standards (33). A dedicated study coordinator will evaluate volunteers to enroll from pregnant patients at the Washington University Medical Center (WUMC) in St. Louis, MO. The Institutional Review Boards of WUMC will approve this study before initiation. A total of eighty consenting women will be randomized to one of two arms POM juice vs POM juice placebo in a 1:1 ratio. The Women’s Health Center at WUMC includes a State-approved collaborative practice of Washington University attending physicians, nurse practitioners, and residents that serve all patients regardless of payer status. The WUMC Center for Advanced Medicine offers a second site for recruitment where university affiliated private practices are located. We anticipate 1-2 patients enrolled per week.

***Treatment group****:* Expecting mothers in this group will be randomized to start a daily regimen of 8 oz glass of pomegranate juice (POM Wonderful). They will keep a daily diary documenting their compliance. They will continue this daily intake up until delivery of their infant.

***Placebo group:***These women will start a daily regimen of an 8 oz of pomegranate free juice placebo that matches taste, calories, and appearance to regular pomegranate juice but lacks polyphenols that contains the same substances without polyphenols. They will also keep a diary of daily intake to help ensure compliance similar to the treatment group. They too will continue to take the placebos up until the time they deliver.

***Both groups:*** All women will be followed up (called) on a weekly basis to assess compliance. Upon delivery, cord blood will be collected and sent for ellagic acid, a polyphenic component. All placental material will be sent for formal pathological exam in addition to the specialized studies outlined below.

Placental Evaluation:

**Overview**: We will test the hypothesis that the active agents in pomegranate extract modulate the villous structure of the placenta, reduces the effects of exogenous stimuli, or both, in the human placenta of women diagnosed to have intrauterine growth restriction.

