**Randomization:**

Mothers will be randomized at the time of enrollment by blinded envelope to either one of the treatment group or a placebo group in a 1:1 ratio.

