**Biostatistical Analyses**

**General methods:**

The statistical methods employed in this study will be complex and will be undertaken with the assistance of [name], biostatistician in the Department of Pediatrics. Clinical data such as maternal risk factors, birth weight, placental weight, gestation, need for resuscitation in the DR, etc. will be collected for both the intervention and the control group during the perinatal course.

The primary outcomes will be either a) brain injury or b) delayed development at 18-24 months. The relationship of placental function and measures to these outcomes will be explored to understand the mechanism of neuroprotection.

Brain injury will be defined as any of the following (see Table 3):

- Moderate to severe injury by qualitative scoring of WMI or GMI
- Diffusion scores (ADC, FA) > 2 SD from normal term infants
- Spectroscopy showing elevated lactate and decreased NAA (hypoxic injury) over the L basal ganglia
- Bottom 25% percentile in brain metrics, volumetric indices, or measures of surface based morphology (SBM) compared to the general healthy population.

Delayed development will be classified as:

- BSID III (MDI or PDI) > 2 SD (< 70) below the normal population

* MRS- MR Spectroscopy; SBM- Surface-based morphology

Table 2. Definition of CNS Injury by US/ MRI

| **Modality** | **Technique** | **Measures** | **Likelihood of injury** | **Definition of**  **Injury** |
| --- | --- | --- | --- | --- |
| Ultrasound |  | Grade IVH | Low | Grade 2-4 |
| MRI | Qualitative | WMI, GMI | Low | Mod-Severe injury |
|  | Diffusion/Spect | ADC, FA  Lactate, NAA | High  Low | > 2 SD above term  Lactate ↑, ↓NAA |
|  | Metrics | Intraparietal diameter, extra cranial space | High | Bottom 25% of the population |
|  | Volumetric | Total volume,  Cerebral gray matter volume, | High | Bottom 25% of the population |
|  | SBM | Cortical surface area, average sucal depth, integrated folding index | High | Bottom 25% of the population |

Continuous variables will be compared using a student t-test when they are parametric and Mann-Whitney test when they are nonparametric. Categorical variables (such as moderate or severe white matter injury) will be compared using either a chi-squared (for parametric) or a Kruskal-Wallis test for nonparametric one way analysis of variance. This is a pilot study where the results will assist in the planning of a larger randomized controlled trial.

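### The protocol names IUGR severity as prognostic and needs a severity measure to apply eligibility, but its arm comparisons are unadjusted, which forgoes some precision

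*Protocol*

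**What the plan says.** Four places in the protocol bear on this.

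- **A potential model.** After reviewing MRI, spectroscopy and long-term follow-up in growth-restricted infants, it says: "These findings are more pronounced when focusing on the more severe end of the IUGR spectrum". The severe end is described as "those with evidence of abnormal umbilical flow (absent or reversed end diastolic flow) or birth weight < 3rd percentile".
- **Inclusion criteria.** A woman enters on an "estimated birth weight ≤ 10th percentile for gestational age and gender based on the Alexander growth curves". There is no lower limit and no Doppler condition, so mild and severe cases are enrolled together.
- **Study plan and Randomization.** Eighty women are allocated 1:1 to two arms: "Mothers will be randomized at the time of enrollment by blinded envelope". No stratification factor is named.
- **Biostatistical Analyses, General methods.** "Continuous variables will be compared using a student t-test when they are parametric and Mann-Whitney test when they are nonparametric". Categorical outcomes get a chi-squared or Kruskal-Wallis test. None of these tests takes a covariate. Clinical data such as birth weight and maternal risk factors are to be collected, but no model uses them in the arm comparison.

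**The concern.** The protocol identifies severity of growth restriction as a driver of outcome, and eligibility cannot be checked without one measure of it. Where a baseline value predicts outcome, a comparison that ignores it treats the variation it explains as noise. That costs little in a large trial. Here there are 40 women per arm and fewer infants scanned, so the loss may be noticeable. It also matters for a pilot, because the General methods section says the results will feed the planning of a larger trial, and less precise estimates make a poorer basis for that.

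**Working it through.** The protocol gives no power, effect size or standard deviation for its 80 women, so there is no figure to reproduce. The check below sizes the loss under stated assumptions.

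**Inputs from the protocol**
- 80 women, 1:1, so 40 per arm.
- MRI completion in the earlier phase was 30 of 41 (preliminary studies). If it repeats, 80 × 30/41 = 58.5 scans, about 29.3 per arm.

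**Assumptions**
- A share p of 20–40% of fetuses is below the 3rd percentile at entry.
- These infants score d = 0.5–1.0 within-stratum SD worse.
- Two-sided alpha is 0.05, and the treatment effect is 0.6 SD (total SD) on a continuous MRI measure.
- The entry estimate carries the full severity effect, with no discount for ultrasound error.

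**Step 1: variance explained by severity.** R² = p(1−p)d² / [1 + p(1−p)d²].

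**Step 2: power.** Normal approximation: power = Φ(0.6 × √(n/2) / √(1−R²) − 1.96), with n = 29.3. Unadjusted, 0.6 × √14.65 = 2.297, and Φ(2.297 − 1.96) = 63.2%.

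| p | d | p(1−p)d² | R² | Power | Gain (points) |
|---|---|---|---|---|---|
| – | – | – | 0 | 63.2% | – |
| 0.2 | 0.5 | 0.0400 | 3.8% | 64.9% | 1.7 |
| 0.3 | 0.5 | 0.0525 | 5.0% | 65.4% | 2.2 |
| 0.4 | 0.5 | 0.0600 | 5.7% | 65.7% | 2.5 |
| 0.2 | 1.0 | 0.1600 | 13.8% | 69.6% | 6.4 |
| 0.3 | 1.0 | 0.2100 | 17.4% | 71.4% | 8.2 |
| 0.4 | 1.0 | 0.2400 | 19.4% | 72.5% | 9.3 |

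In sample-size terms, 1/(1−R²) runs from 1.04 to 1.24. Adjusting 58.5 scans is worth about 61 (58.5 × 1.04) to 73 (58.5 × 1.24) unadjusted scans.

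**Step 3: chance imbalance.** With two independent Bin(40, p) counts, the arms differ by at least 6 of 40 (15 percentage points) in severe cases in 12.3%, 17.9% and 20.9% of randomisations for p = 0.2, 0.3 and 0.4. With arms fixed at 40 (hypergeometric), the figures are 16%, 22% and 25%. A 15-point gap shifts the unadjusted difference by 0.15 × d, that is 0.08–0.15 SD. The standard error of the arm difference at 29.3 per arm is √(2/29.3) = 0.26 SD. The shift lies well inside it and is part of the sampling variation the test already allows for.

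**The case against.** **Validity.** A reader might infer that unstratified allocation biases the trial, or that imbalance is a second harm on top of lost precision. Neither follows. Simple 1:1 randomisation keeps the test valid, and step 3 shows that the imbalance is the same cost seen from another side.

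**Severity and MRI.** A reader might also take the background as stating outright that severity worsens term MRI. The sentence directly follows the one on cerebral palsy, learning, cognition and attention, and the titles of references 29–31 concern school age, age 7 and adolescence. The MRI findings come earlier in the paragraph, with their own references. The link to MRI is a reasonable reading and not an explicit statement. The link to later development is direct, and development at 18–24 months is also a primary outcome.

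**The marker.** The background names birth weight below the 3rd percentile, whereas the trial holds an ultrasound estimate at entry. The documents do not say how well that estimate predicts outcome, and measurement error would lower R². This objection stands, and it favours the lower end of the table.

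**The outcome.** The primary outcomes are binary classifications, while the power figures are for a continuous MRI measure. This stands too: no gain has been shown for the binary outcomes.

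**Left to the SAP.** Covariates are often chosen in the SAP, and the protocol does not rule out adjusted models. However, the section does more than stay silent, since it names the tests and all are unadjusted. An adjusted analysis introduced later would depart from the written plan.

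**Pilot status.** There is no power target to miss, which limits the weight of the point. The change is nonetheless nearly free.

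**Conclusion.** The point holds as a modest loss of precision. Severity is named as prognostic, a measure of it is needed before randomisation, and the stated comparisons do not use it. Under the assumed 20–40% severe share and 0.5–1.0 SD gap, severity accounts for about 4–19% of variance, and adjustment lifts power from about 63% to 65–73% for a 0.6 SD effect on a continuous MRI measure. At a 0.5 SD gap the gain is only about 2 points. The severe share, the gap and the effect size are all assumptions, since the documents give none of them. The documents do not support a claim of bias, of type I error inflation, or of a sizeable gain across the whole assumed range.

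**What to change.** In Biostatistical Analyses, replace the unadjusted t-test for the continuous MRI measures and the 18–24 month Bayley scores with a linear model containing treatment arm and the estimated-weight percentile at enrolment, specified before any unblinded look at the data. Use the enrolment value and not birth weight, which is measured after the juice has started and could be affected by it.

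Two additions are optional. If envelopes are not yet prepared, they could be split into two strata (below the 3rd percentile, and 3rd to 10th), with the stratum kept in the model. Where umbilical Doppler at entry is available from clinical care, it could be recorded as a second covariate; it is not on the current list of data to be collected.

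The cost is one extra model term using a value already needed for eligibility and, if stratified, a second set of envelopes. The downside is that the gain will be small if entry severity predicts outcome only weakly.

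### Continuous MRI brain-size outcomes are compared with unadjusted two-sample tests, and no entry ultrasound measurement is recorded for adjustment; the tests are valid, but precision is lost

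*Protocol*

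**What the plan says.** Entry requires a fetal diagnosis of growth restriction, "defined by estimated birth weight ≤ 10th percentile for gestational age and gender based on the Alexander growth curves", at least 6 weeks before the due date (Protocol, Inclusion criteria). The Background says that most such infants are "diagnosed prenatally by standardized ultrasound measurements (usually end of the 2nd trimester"), so a prenatal measurement precedes randomisation. It also says that growth-restricted premature infants have smaller intracranial, gray matter and hippocampal volumes on MRI.

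The Study plan states that "A total of eighty consenting women will be randomized to one of two arms" in a 1:1 ratio. Under Randomization, "Mothers will be randomized at the time of enrollment by blinded envelope"; no stratification factor is named.

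The MRI Evaluation section schedules one scan at 38-41 weeks, giving brain metrics, volumes and surface measures. For the comparison of arms, General methods says: "Continuous variables will be compared using a student t-test when they are parametric and Mann-Whitney test when they are nonparametric". It names no covariate. Neither the perinatal data list nor the clinical data listed under General methods includes fetal head size, the estimated fetal weight percentile or gestation at entry.

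The Figure 5 caption, which begins "Brain Metrics representing brain growth demonstrated that infants who had pomegranate exposure in their mothers had larger biparietal diameters", describes the earlier pilot against apple juice. It shows how the investigators interpret these measures. It is not the analysis plan for this trial.

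**The concern.** Size at term is the sum of growth before the first glass of juice and growth afterwards. The juice cannot have changed the first part, yet variation in that part stays in the residual variance of a two-sample comparison. Entry may fall at any time up to 6 weeks before the due date, so the share of growth that precedes treatment also differs between women.

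A pre-randomisation measurement related to the outcome is available for a trial with few scans, and the stated method does not use it. Because the protocol itself picks the tests and lists the data items, this is not only a detail left for a later analysis plan. A covariate that was never captured at enrolment may not be recoverable when that plan is written. At stake are the precision of the continuous MRI size comparisons and the variance estimates that this pilot is meant to hand to a larger trial.

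**Working it through.** **Inputs from the protocol**
- 80 women, 1:1, so 40 per arm (Study plan).
- In the pilot, 30 infants were scanned from 41 mothers randomised (Background).
- Continuous outcomes: t-test or Mann-Whitney, no covariate (General methods).

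**Assumed, because the protocol does not give them**
- Two-sided alpha 0.05.
- A true difference of 0.5 SD between arms.
- Correlation r between the entry measurement and term brain size of 0.3, 0.5 or 0.7. It probably differs between measures.

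The protocol gives no alpha, power, effect size or SD, so the total of 80 cannot be reproduced.

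**Scans available.** If pilot scan loss recurs, 80 × 30/41 = 58.5, or about 29 per arm.

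**Variance removed.** ANCOVA on the entry value leaves residual variance 1 − r²:
- r = 0.3: 0.91, so 9% is removed; 29/0.91 = 31.9, as if 32 per arm.
- r = 0.5: 0.75, so 25% is removed; 29/0.75 = 38.7, as if 39 per arm.
- r = 0.7: 0.51, so 49% is removed; 29/0.51 = 56.9, as if 57 per arm.

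**Power.** The noncentrality is 0.5/√(1 − r²) × √(29/2), where √14.5 = 3.808. The critical t is 2.003 on 56 df unadjusted and 2.004 on 55 df with one covariate.

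| Analysis, 29 per arm | Noncentrality | Power at 0.5 SD | Difference detectable at 80% power |
| --- | --- | --- | --- |
| Unadjusted t-test | 1.904 | 46.5% | 0.75 SD |
| ANCOVA, r = 0.3 | 1.996 | 50.0% | 0.71 SD |
| ANCOVA, r = 0.5 | 2.198 | 57.9% | 0.65 SD |
| ANCOVA, r = 0.7 | 2.666 | 74.5% | 0.54 SD |

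If all 40 per arm were scanned, the same formula gives 60% unadjusted, against 64%, 72% and 87%.

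**Check by simulation** (4000 runs for each r, 29 per arm, entry values drawn at random in each arm).
- The unadjusted estimate averaged 0.49 to 0.50 for a true 0.5, and its type I error was 4.5% to 5.2%. The stated test is therefore valid.
- Its power was about 46%, against 49%, 56% and 73% for ANCOVA. The ANCOVA figures are 1 to 2 points below the table, mainly because the formula ignores the small cost of adjusting for chance imbalance in the covariate.

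**The case against.** The strongest reply is that nothing here is an error. The arms are randomised, the two-sample test is unbiased, and the choice of covariates often belongs in an analysis plan, which may exist. General methods also says that the methods will be complex and undertaken with a biostatistician, and it does not rule out adjusted models. The first part stands in full: the issue is efficiency, not validity. The second stands only in part, because the protocol names the tests and leaves the entry measurement off its data lists.

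Three stronger readings are tempting, and the protocol does not support them.
- **Bias.** A reader might infer that a deficit present at entry biases the comparison, or that chance imbalance is a further hazard. With 29 per arm the chance of an entry difference above 0.3 SD is about 25% (standard error √(2/29) = 0.263). That variation is already inside the standard error and the 5% error rate of the t-test, and must not be counted again.
- **Head size known to be small at entry.** Entry is by estimated weight. The reduced volumes cited in the Background come from postnatal MRI. The statement that "this neuroprotection is specific to polyphenols and is only present when given prior to the insult" comes from animal work, and the Background describes repeated hypoxemia and poorly tolerated labor, so insults after entry remain possible. The protocol also does not say that head size is recorded.
- **A large gain.** No correlation is given. At 0.3 the gain is small, and nothing shows that an entry head measurement predicts folding or sulcal depth as well as it might predict overall size.

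It is also fair to say that a linear model on continuous measures leaves the primary outcomes, brain injury and delayed development, as they are, since both are categorical.

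**Conclusion.** The point holds as a modest matter of precision. The protocol fixes unadjusted tests for the continuous MRI size measures and does not retain a pre-randomisation value that could reduce their variance. With about 29 scans per arm and an assumed 0.5 SD difference, power is about 47% as planned, against about 50% to 75% with ANCOVA over assumed correlations of 0.3 to 0.7. The low end is nearly negligible and the high end substantial; the protocol does not say which applies. The result rests on pilot scan loss recurring and on a usable entry measurement being available. No bias, inflated error rate or effect on the primary outcomes is claimed. Because General methods describes a pilot meant to plan a larger trial, the adjusted variance and the entry-to-term correlation would be useful results in themselves.

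**What to change.** - Add to the data collected at enrolment, from the qualifying ultrasound: the estimated fetal weight percentile, gestation at entry and, where reported, head measurements as z-scores for gestational age.
- In General methods, compare the continuous brain metrics, volumes and surface measures between arms by ANCOVA with the entry head-size z-score as covariate. Use the estimated-weight z-score if head size is unavailable, and state that rule in advance.
- Keep the t-test or Mann-Whitney as sensitivity analyses.
- Report the entry-to-term correlation and residual SD for each measure, for planning the larger trial.

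The cost is a few values copied from an examination already done for eligibility, a missing-value rule, and one or two degrees of freedom. No visit or procedure is added, and the definitions of the categorical primary outcomes do not change.
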